### Primary endpoint

#### 2.5-year metastases progression-free survival (MPFS)

MPFS is defined as the time from randomisation to the date of metastases progression (appearance of new metastatic recurrence and/or progression of the treated metastases), reported by PSMA PET/CT during the follow-up (date PSMA PET/CT).

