### Secondary endpoints

#### Sensitivity of the PSMA PET/CT for detecting oligometastases and pattern of recurrences after MDRT

##### Biochemical Progression-Free Survival (bPFS)

bPFS is defined as the time from the date of randomisation to the date of biochemical (PSA) recurrence. In this study a PSA-value higher than the last value prior to therapy (validated 6 weeks later) is considered a secondary biochemical recurrence (post MDRT BCR).

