##### Clinical progression-free survival (PFS)

Progression is defined as biochemical progression, clinical progression (including loco-regional or distant progression on imaging) or start with hormonal therapy, whichever occurs first.

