##### Time to palliative hormonal treatment (ADT)

Time to hormonal treatment is defined as the time from trial randomisation to start of palliative hormonal treatment. Palliative ADT should not be started for biochemical progression without documented clinical progression. In case of symptomatic progression, palliative ADT is mandatory. In case of clinical asymptomatic progression, delayed ADT until progression to a symptomatic state is permitted for men who are well informed (EAU guidelines [1]).

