##### Overall survival

Overall survival is defined as the time from the date of randomisation to the date of death from any cause.

*Other secondary endpoints* are disease specific survival, start of second-line treatment, start of second MDRT treatment for new (progressive) oligometastases, and the time to castration-resistance.

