#### Androgen deprivation therapy (arm 2)

The experimental arm should receive an LHRH-agonist (leuprorelin), for a duration of 6 months. The medication will be given in one administration of 45 mg (subcutaneously), the leuprorelin will be supplied on a physician prescription and administered according to the standard use of this medication for prostate cancer. Flare prevention with an anti-androgen could be used for at least 5 days prior to the first injection of the agonist and should not be continued for longer than 28 days. ADT should start no later than the first day of radiotherapy and no earlier than 12 weeks before the start of radiotherapy. Testosterone levels should be checked at 4 weeks following the first injection. ADT-related toxicity should be managed according to Nguyen et al [20].

No treatments potentially influencing the PSA level should be started before the primary endpoint is reached (metastatic progression). The total duration of ADT is limited to 6 months and is not allowed to be continued afterwards. It is highly recommended not to start ADT in case of biochemical progression without clinical progression.

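### PFS counts the start of hormonal therapy without excepting the randomised ADT, and MPFS and bPFS are named as survival endpoints although their stated events omit death

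*Protocol article*

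**What the plan says.** All references are to the protocol article.

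- **Primary endpoint.** "MPFS is defined as the time from randomisation to the date of metastases progression", that is, new metastases or progression of treated ones, "reported by PSMA PET/CT during the follow-up (date PSMA PET/CT").
- **bPFS.** "bPFS is defined as the time from the date of randomisation to the date of biochemical (PSA) recurrence".
- **Clinical PFS.** Progression is biochemical progression, clinical progression, "or start with hormonal therapy, whichever occurs first".
- **Time to palliative hormonal treatment**, a separate secondary endpoint. "Time to hormonal treatment is defined as the time from trial randomisation to start of palliative hormonal treatment".
- **Overall survival.** "Overall survival is defined as the time from the date of randomisation to the date of death from any cause".
- **Androgen deprivation therapy (arm 2).** "The experimental arm should receive an LHRH-agonist (leuprorelin), for a duration of 6 months", and "ADT should start no later than the first day of radiotherapy and no earlier than 12 weeks before the start of radiotherapy".
- **Exclusion criteria.** Patients who have had ADT for recurrent disease are not eligible.
- **Primary endpoint analysis.** Observations are censored at 30 months and the arms are compared by Cox regression. The section does not say how a death before progression is treated.

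**The concern.** **Clinical PFS.** The start of hormonal therapy is a sensible progression event only if it means therapy given because the disease has progressed. In this trial hormonal therapy is also the randomised treatment, and the definition does not separate the two. An analyst who follows the text would record an event at treatment start for the whole treated experimental arm.

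**MPFS and bPFS.** A reader takes the 2.5-year figure of an endpoint called progression-free survival as the proportion alive without progression. With the events listed, a patient who dies without PET/CT progression contributes no event. If such deaths were censored, the Kaplan-Meier proportion would be too high for the quantity that its name promises. The primary endpoint is presented as a 2.5-year figure, and the sample size is built on a published median progression-free survival, so the planned and observed quantities need the same event definition.

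**Working it through.** **1. Clinical PFS: the sections side by side**

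- The PFS event is any start of hormonal therapy, with no qualifier.
- Arm 2 starts an LHRH agonist by the first radiotherapy day at the latest.
- Earlier ADT for recurrent disease is an exclusion criterion, so the assigned drug is a new start.
- The separate hormonal-treatment endpoint is limited to palliative treatment. The article makes the distinction there and does not carry it into PFS.

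Hence, as written, each arm-2 patient who receives the assigned drug has an event by the first radiotherapy day: up to 140 of 140, with arm-2 PFS near 0% when treatment begins. No formula is needed.

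**2. The plan's own sample size**

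Inputs from the Sample size section: hazards 0.0330 and 0.0205 per month, HR 0.621, alpha 5% (taken as two-sided), power 80%, dropout 18% at 30 months.

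- Event-free at 30 months: exp(−0.0330 × 30) = 37.2% and exp(−0.0205 × 30) = 54.1%. The stated 37.1% and 54.0% agree up to rounding of the hazards.
- Schoenfeld events: 4 × (1.960 + 0.842)² / (ln 0.621)² = 138.3, so 139.
- Dropout as exponential censoring: g = −ln(0.82)/30 = 0.00662 per month.
- Event probability per arm: h/(h+g) × (1 − exp(−30(h+g))) = 0.579 and 0.421, mean 0.500.
- N = 139/0.500 = 278, or 139 per arm against 140 stated. Power at 280 is 80.5%.

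The sample size reproduces. It rests on one progression hazard per arm, with no separate death component.

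**3. How many patients the omission of death could affect**

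The article gives no mortality figure. Assume 1–3% per year of deaths without documented progression, equal in both arms. Only patients still progression-free can be affected.

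- Mean progression-free time within 30 months, (1 − exp(−30h))/h: 0.6284/0.0330 = 19.0 months and 0.4594/0.0205 = 22.4 months.
- Person-time: 140 × (19.04 + 22.41)/12 ≈ 484 person-years, before any dropout.
- Deaths: 484 × 0.01 ≈ 5 to 484 × 0.03 ≈ 15.

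Overstatement of the 30-month proportion if deaths are censored, S(30) × (1 − exp(−2.5r)) for yearly rate r:

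| Arm | r = 1% | r = 3% |
|---|---|---|
| MDRT | 37.2% × 0.0247 = 0.9 points | 37.2% × 0.0723 = 2.7 points |
| MDRT + ADT | 54.1% × 0.0247 = 1.3 points | 54.1% × 0.0723 = 3.9 points |

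**4. Power if death is counted as an MPFS event**

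For an assumed 30-month mortality m, add d = −ln(1 − m)/30 to both hazards. The HR becomes (0.0205 + d)/(0.0330 + d). Repeat step 2.

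| m | HR | Power at N = 280 | Per arm for 80% |
|---|---|---|---|
| 1% | 0.625 | 79.7% | 142 |
| 2% | 0.629 | 79.1% | 144 |
| 5% | 0.640 | 77.0% | 152 |
| 10% | 0.658 | 73.3% | 165 |

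The 1–3% per year of step 3 corresponds to 2.5–7.2% at 30 months (1 − exp(−2.5r)), inside this range. If deaths are censored instead, the HR stays at 0.621 and power runs from 80.3% to 78.8% as m goes from 1% to 10%.

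**The case against.** **The PFS point rests on a literal reading.** Hormonal therapy is listed there as a form of progression, the neighbouring endpoint says palliative, and the ADT section keeps the assigned course apart from ADT started later for progression. Nobody plausibly intends to count the assigned drug. That stands as to intent. It does not repair the text, and in a trial that randomises ADT the event rule should not depend on a guess. A reader might infer that the trial will report a reversed PFS result; the document supports only that the rule, if followed as written, makes the comparison unusable.

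**Time to metastatic progression is a legitimate endpoint.** This stands. The planned primary analysis is a Cox hazard ratio, and with deaths censored that is a valid cause-specific hazard ratio. A reader might infer that the primary endpoint or its test is wrong. What is wrong is narrower: the name and the 2.5-year proportion do not match the listed events.

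**Censoring of deaths is not stated.** This also stands. The article gives censoring at 30 months and no rule for death, and such rules are commonly left to the full protocol or SAP. The omission of death from the stated MPFS and bPFS events is nevertheless in the text.

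**PFS may include death.** The clinical PFS section defines progression, not the full time-to-event variable. It is silent on death and does not exclude it, so the death point should not be extended to PFS.

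**Harms of the drug are captured elsewhere.** Toxicity, overall survival and disease-specific survival are separate endpoints, so it would be wrong to say that the trial ignores them.

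**Conclusion.** Both parts hold in limited form.

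The PFS definition is unusable as written, because it makes the assigned treatment an event in arm 2. This concerns one secondary endpoint and is cured by a short exclusion.

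The MPFS and bPFS definitions do not match their names. For the primary endpoint the effect is modest: about 5–15 of 280 patients and about 1–4 points on the 2.5-year proportion. That rests on an assumed 1–3% per year of deaths without progression, equal mortality in the two arms, the article's own hazards, and deaths being censored. A count of 280 × 2.5 years × 1–3%, or 7–21 patients, is tempting but too high, because it keeps patients at risk after they have progressed. The stated sample size reproduces and is not in dispute.

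**What to change.** **Clinical PFS.** Define the hormonal event as the start of hormonal therapy other than the protocol-assigned ADT. This is one phrase and has no downside.

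**MPFS and bPFS.** Choose one of two routes, before outcome data are seen.

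1. Add death from any cause as an event, keep the progression-only analysis as a sensitivity analysis, and restate power. The cost is dilution of the HR by deaths unrelated to treatment and the loss of power shown above. It also changes the primary event of an open trial in which 100 patients were already randomised by December 2021.
2. Rename them as time to metastatic and time to biochemical progression, state how death is handled, and report the 2.5-year figure as cumulative incidence with death as a competing event. The cause-specific Cox model and the present sample size can stay. The cost is that the primary result no longer describes progression-free survival, so overall survival must be read beside it.

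In the same edit, state whether death counts as an event in clinical PFS. Neither route changes treatment or visits.

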### Secondary endpoints

#### Sensitivity of the PSMA PET/CT for detecting oligometastases and pattern of recurrences after MDRT

##### Biochemical Progression-Free Survival (bPFS)

bPFS is defined as the time from the date of randomisation to the date of biochemical (PSA) recurrence. In this study a PSA-value higher than the last value prior to therapy (validated 6 weeks later) is considered a secondary biochemical recurrence (post MDRT BCR).

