### Evaluation and follow-up

At baseline the investigations include the collection of patient characteristics, a full medical history including PCa characteristics, and the results of the PSMA PET/CT imaging. Baseline toxicity (physician and patient reported) and QoL (patient reported) are recorded. Baseline laboratory assessments include PSA, Testosterone, Haemoglobin (Hb), and Alkaline phosphatase (ALP). The assessments at follow-up include changes in medical history and medication, WHO-performance score, and regular laboratory assessments. Toxicity and QoL will be regularly monitored, and adverse events are reported. The investigations required at baseline and during follow-up are summarized in Table 2.

**Table 2 Tab2:** Follow up after radiotherapy treatment

Required investigation	Baseline	Treatment period		Follow-up				
			1 m after RT	3 m after RT	6 m after RT	9 m after RT	12 m after RT	Every 6 (up to 36 months) months until progression^b^
Eligibility check	X							
Informed consent	X							
ADT (arm 2)		X						
Patient characteristics/ medical history	X		X	X	X	X	X	X
Laboratory assessment								
PSA	X		X	X	X		X	X
Testosterone	X		X		X		X	X
Hb	X			X	X		X	X
ALP	X			X	X		X	X
Whole body PSMA PET/CT^a^	X						X	Every 12 months
Treatment and dosimetric data		X						
Toxicity & QoL								
CTCAE v4	X	X^c^	X	X	X		X	X
RTOG-EORTC toxicity	X	X^c^	X	X	X		X	X
EORTC-QlQ-25	X				X	X	X	X
EORTC-QLQ-C-30	X				X		X	X
SAE		X	X	X	X	X	X	X^d^

^a^ PSMA before inclusion, at progression and for patients without progression only at 12 and 24 months

^b^ 36 months visit, only lab, EORTC-QLQ-C-30 and CTCAE toxicity criteria

^c^ only in case of WPRT or prostate bed RT, the toxicity measurements should be intended at 4th week of treatment course

^d^ Until 2.5 years after treatment completion

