#### Imaging

Follow-up PSMA PET/CT should be performed in case of biochemical progression and for patients without progression at 12 and 24 months after treatment. Biochemical progression is defined as a PSA-value higher than the last value prior to therapy (validated 6 weeks later).

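### bPFS counts only a confirmed PSA rise, so men salvaged after a routine scan finds metastases first are left event-free or informatively censored, possibly to a different degree in each arm

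*Protocol article*

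**What the plan says.** In the protocol article, the section on biochemical progression-free survival defines the endpoint: "bPFS is defined as the time from the date of randomisation to the date of biochemical (PSA) recurrence". The qualifying event is given there too: "a PSA-value higher than the last value prior to therapy (validated 6 weeks later) is considered a secondary biochemical recurrence". Nothing else ends bPFS.

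Four other parts of the article bear on what happens to a man before that event:

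- Imaging: "Follow-up PSMA PET/CT should be performed in case of biochemical progression and for patients without progression at 12 and 24 months after treatment". The scans at 12 and 24 months therefore fall on men who have not met the PSA rule.
- Androgen deprivation therapy (arm 2): "No treatments potentially influencing the PSA level should be started before the primary endpoint is reached (metastatic progression". The restriction ends once metastases have progressed.
- Time to palliative hormonal treatment: "In case of symptomatic progression, palliative ADT is mandatory", while delay is permitted in asymptomatic clinical progression. The other secondary endpoints include "start of second MDRT treatment for new (progressive) oligometastases".
- Table 2 heads the later visits, which include PSA, "Every 6 (up to 36 months) months until progression".

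The separate clinical PFS is broader: "Progression is defined as biochemical progression, clinical progression (including loco-regional or distant progression on imaging) or start with hormonal therapy, whichever occurs first". Time-to-event secondary endpoints are to be compared by Cox regression adjusted for the stratification variables. The Abstract lists bPFS among the secondary endpoints.

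**The concern.** The protocol itself creates men who progress without a bPFS event. Take an invented record: PSA 3.0 before therapy, 0.3 at 6 months and 1.5 at 12 months. The 12-month scan shows new bone lesions and second MDRT is given. PSA is 0.4 at 18 months, if it is measured at all. He has progressed and been salvaged, yet he never exceeds 3.0.

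Two readings are open. If PSA is followed on, he is event-free, but on a PSA that now reflects the salvage rather than the randomised treatment. If follow-up stops at progression, as Table 2 suggests, he is censored at the moment he progresses. Cox regression needs censoring that is unrelated to the risk of the event. A man with new metastases is not at average risk of a PSA rise, so this censoring is informative.

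Arm 2 alone receives a drug that suppresses PSA, so the share of progressors found by scan first may differ between arms. A bPFS contrast could then partly reflect which signal came first.

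**Working it through.** **Inputs from the article.** Sample size section: hazards of 0.0330 and 0.0205 per month, hazard ratio 0.621, alpha 5%, power 80%, dropout 18% at 30 months. Imaging section: routine scans at 12 and 24 months. Table 2: PSA visits. The article gives no duration of PSA suppression after ADT, no PSA kinetics and no planning figure for bPFS.

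**The plan's own figures first.** ln 2/21 = 0.0330; −ln 0.65/21 = 0.0205; ratio 0.621. Schoenfeld events (two-sided 5%): 4(1.960 + 0.842)²/(ln 0.621)² gives 139. With exponential dropout δ = −ln 0.82/30, P(event) = λ/(λ+δ) × [1 − exp(−30(λ+δ))], which averages 0.500 over the arms. N = 139/0.500 = 278, against the stated 280. The hazards are sound, and nothing here touches the sample size.

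**Check 1: which arm has more scan-first progressors?** Metastases are exponential at the design hazards. Assumed: the PSA rise lags metastasis by a mean of 3, 6 or 12 months, and ADT holds PSA below the reference until month D in every arm-2 man. Scan-first means found on the 12- or 24-month scan before the PSA event. Entries are MDRT / MDRT + ADT.

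| Suppression | Lag 3 | Lag 6 | Lag 12 | bPFS HR, PSA only | HR, scan progression counted |
|---|---|---|---|---|---|
| D = 0 or 9 months, % of men | 12/9 | 22/16 | 33/24 | 0.60–0.68 | 0.61–0.63 |
| D just past the 12-month scan, % of men | 12/26 | 22/29 | 33/32 | 0.28–0.31 | 0.61–0.62 |
| D just past the 12-month scan, % of progressors | 20/60 | 38/70 | 59/80 | as above | as above |

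With equal metastatic hazards and D past 12 months, the PSA-only HR is 0.36–0.45, against 0.97–1.00 when scan progression counts. Part of each low PSA-only HR is the drug's direct delay of the PSA rise, so the difference is not all bias. A floor on PSA in every man is an extreme assumption and gives a bound, not an estimate.

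**Check 2: separating the direct PSA delay from the bias.** Assumed PSA crossing time = doubling time × log2(1/nadir fraction) + delay. Median nadir is 30% of the pre-therapy value (log-SD 0.8), median doubling time 6 months (log-SD 0.5), and the delay is 0 in arm 1 and 6 or 9 months in arm 2. Metastases occur at 0.033 per month in both arms. With PSA and metastases independent, 30-month event rates are:

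| Handling of scan-first men | Arm 1 | Arm 2 (delay 6 / 9) | Gap, points |
|---|---|---|---|
| True PSA event | 94% | 89% / 85% | 5–9 |
| Censored at the scan | 94% | 89% / 85% | 5–9 |
| Never counted | 82% | 68% / 59% | 14–23 |
| Counted as events | 97% | 95% / 93% | 2–4 |

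Under independence, censoring does no harm. With an assumed correlation of 0.6 between the PSA crossing time and the metastasis time, the true gap is still 5–9 points, but it becomes about 7–14 under censoring and 15–27 if the men are never counted. From these rounded figures the distortion is 7 − 5 = 2 to 14 − 9 = 5 points under censoring, and 15 − 5 = 10 to 27 − 9 = 18 points if never counted.

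**Sensitivity (independent model).** With the arm-2 design hazard of 0.0205, scan-first men are 19% (6-month delay) or 23% (9-month delay) of arm 2, against 15% of arm 1. With no PSA delay they are 11% against 15%, so the direction reverses. If only half of salvages suppress PSA (hazard 0.033 in both arms), the never-counted rates are 88% against 78% / 72%, a gap of 10 to 16 points.

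**The case against.** The strongest reply is that this is silence rather than error. Censoring rules for a secondary endpoint usually sit in the analysis plan, which is not shown, and the article nowhere says that salvaged men are scored event-free. That stands as far as censoring goes. The event list, however, is fixed in the article, and no censoring rule adds an event to it. Both ways of applying the definition have the fault described.

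Second, check 2 shows unbiased censoring when PSA and metastases are independent. This is correct, but independence is hard to defend in a protocol that uses a PSA rise as the trigger to look for metastases.

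Third, MPFS dates these men at the scan, and clinical PFS counts imaging progression and hormonal therapy. A PSA-only endpoint beside a composite is a legitimate choice. This stands and limits the importance. It does not make the bPFS contrast readable by itself.

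Fourth, not every scan-first man will be salvaged at once, since the article permits delayed ADT in asymptomatic progression. This stands, and it makes the never-counted figures upper-end.

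Two stronger readings are tempting. A reader might infer that scan-first progression is more frequent in the ADT arm and that bPFS therefore favours it. The article does not support this: it gives no suppression time, and check 1 shows fewer such men in arm 2 when suppression is short and ADT works as designed. A reader might also suppose that treatment could start after a PSA-triggered scan but before the 6-week repeat, so that the rise is never validated. The Imaging section defines the trigger as a rise already validated, so following the protocol does not produce that case.

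**Conclusion.** The point holds in limited form. The bPFS definition omits salvage that the protocol foresees before PSA recurrence. Affected men are counted on a salvage-altered PSA or censored informatively, and the bias may differ by arm.

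Its direction and size cannot be fixed from the article. It may favour MDRT + ADT if PSA suppression lasts past the 12-month scan, and may be small or reversed if it does not. The illustrative distortion of about 2 to 5 points under censoring, or 10 to 18 if never counted, rests on equal metastatic hazards, a correlation of 0.6, a 6- to 9-month PSA delay in arm 2, and salvage at the scan in every scan-first man. Nor should the gap of 14–23 points against 2–4 in the independent model be read as the bias: a true PSA gap of 5–9 points is already present, and counting these men as events changes the quantity measured.

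Only a secondary endpoint is affected. MPFS and the sample size are not.

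**What to change.** In the bPFS section, define the event as the first of: a validated PSA above the last pre-therapy value; start of palliative ADT; start of second MDRT or other salvage for progression. State that the randomised 6-month ADT is not an event.

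Report the PSA-only version as a sensitivity analysis with salvage as a competing event. Show cumulative incidences of both PSA recurrence and salvage by arm, because a Cox model that simply censors at salvage would repeat the difficulty. Tabulate by arm the men whose metastases were found by scan first, including those not treated at once. They remain at risk under this definition, and the analysis plan should say how their later PSA values are used.

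The cost is endpoint wording. Starts of palliative ADT, second MDRT and second-line treatment are already secondary endpoints, so their dates should be at hand. The downside is that bPFS moves closer to clinical PFS, and any ADT benefit on it may look smaller. No change to sample size or patient management is needed.
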